# Does luteal phase support in MOH-IUI treatment improve cumulative live birth rates in couples with unexplained subfertility? Study protocol of the LUMO study: a multicentre, randomised, double-blind, controlled trial with cost-effectiveness analysis

**DOI:** 10.1136/bmjopen-2025-111872

**Published:** 2025-11-19

**Keywords:** Reproductive medicine, Subfertility, Randomized Controlled Trial

## Abstract

**Introduction:**

Couples diagnosed with unexplained subfertility are advised to start mild ovarian hyperstimulation and intrauterine insemination (MOH-IUI) as a primary treatment. Natural feedback mechanisms and hormone release are affected by artificially stimulated cycles and induced ovulation. Additional luteal support could positively affect progesterone patterns in the luteal phase. The LUMO study evaluates whether the addition of exogenous progesterone in the luteal phase following MOH-IUI treatment cycle will improve pregnancy and live birth rates.

**Methods and analysis:**

A multicentre randomised, double-blind, controlled trial will be conducted in Dutch fertility clinics, academic and non-academic hospitals. There are two treatment arms: group A progesterone luteal phase support; group B placebo, without crossover. All initiated MOH-IUI cycles within 6 months after randomisation are included (study period). Participants will start study medication, applying a daily dosage of 2dd 300 mg progesterone (Utrogestan) or 2dd 300 mg placebo in vaginal capsules on the second day after the IUI procedure. Treatment is continued until the onset of menstruation, a negative pregnancy test (IUI+14 days), a miscarriage or until 7 weeks of gestation in case of a viable pregnancy. Follow-up ends at 12 months after the end of study period (18 months after study randomisation). The primary outcome is cumulative pregnancy rate, achieved within 6 months after randomisation, leading to live birth. A total of 1008 patients (504 patients in each group) will be included.

**Ethics and dissemination:**

The study was approved by the Central Committee on Research Involving Human Subjects on 30 January 2023. All participating sites have the approval of the local Board of Directors to participate in the LUMO study. An informed consent form will be signed by all participants. Study results will be presented at (inter)national conferences and published in peer-reviewed journals. It is expected that the results of this trial will be used to draft national guidelines on this issue.

**Trial registration number:**

The study is registered in the EU CTIS trial register (2022-501534-33-00), the Dutch trial registry (registration number: LTR 24508), ClinicalTrials.gov (NCT05080569) and the WHO registry (universal trial number: U1111-1280-9461).

STRENGTHS AND LIMITATIONS OF THIS STUDYThis is the largest randomised trial investigating the efficacy of the addition of luteal phase support in mild ovarian hyperstimulation and intrauterine insemination (MOH-IUI) treatment.This trial follows a double-blind, placebo-controlled design to ensure that neither the participant will be influenced in her behaviour by knowing which ‘medication’ she uses, nor the doctor or nurse administering the MOH-IUI treatment is biased in their actions.Although the use of micronised progesterone is proven to be safe during (early) pregnancy and the LUMO trial is considered a low-risk clinical trial, participants will receive an online medication diary at the start of every cycle and a questionnaire at the end of the study period about any side effects and other issues to closely track the safety of the study participants.Complete adherence to the study protocol cannot be assured as participants are not required to return unused study medication to their study team.

## Introduction

 During the natural female cycle, hormone production is regulated by feedback mechanisms. Follicle-stimulating hormone (FSH) triggers growth and maturation of a dominant follicle during the follicular phase. Oestrogen levels progressively increase and during a final rapid increase, feedback mechanisms occur that elicit a surge of luteinising hormone (LH) and FSH secretion from the pituitary, inducing final maturation and ovulation of the oocyte. Driven by intensified LH release, the corpus luteum produces progesterone during the luteal phase which allows endometrial secretory transformation and promotes endometrial receptivity, critical for implantation of the developing blastocyst and maintenance of (early) pregnancy.^1^,^8^

The hormone release from the developing follicle(s) and the natural feedback mechanisms may become altered in artificially stimulated cycles and induced ovulation. Supraphysiologic serum steroid levels during the ovarian stimulation phase may cause pituitary inhibition, thereby suppressing the natural release of LH.^9^,^11^ The single-dosage human chorionic gonadotropin (hCG) that is injected as an ovulation trigger will induce a stronger pathway than produced by the normal spontaneous LH surge. The corpus luteum is adequately supported by the exogenous LH-like signal during the first days of the luteal phase until this signal is cleared with the resorption of the hCG trigger after approximately 5–6 days. Without additional support, progesterone levels tend to drop considerably and earlier compared with the natural progesterone pattern.^10^ Both the early peak and later defective progesterone secretion may lead to premature or even insufficient arrival into the receptive state of the endometrium and insufficient maintenance of endometrium function thereafter. All this may result in failure of embryo implantation and growth.^12^ Luteal phase support (LPS), by administering exogenous progesterone, has been previously proven to positively affect the level of progesterone and the length of the luteal phase.^13^

Intrauterine insemination (IUI) is a widely used fertility treatment in couples diagnosed with unexplained or mild male subfertility. Mild ovarian hyperstimulation (MOH), applying a low dosage of gonadotropins (eg, FSH), letrozole or clomiphene citrate (CC), is generally used to achieve growth of one or two dominant follicles. A single dose of hCG (often Ovitrelle 250 µg) is used as an exogenous trigger to complete final oocyte maturation and induce ovulation. Subsequently, prewashed semen is injected into the uterus at approximately 24–42 hours after the hCG trigger.^14^ Annually, approximately 9500 couples enter a MOH-IUI infertility treatment programme in the Netherlands (based on Dutch Care Authority (NZA) documentation).^15^

Currently, there is no consensus on the use of progesterone supplementation after MOH-IUI. A meta-analysis by Green *et al* in 2017 concluded that LPS could be effective in MOH-IUI, specifically in mild stimulation cycles using low-dose FSH, with live birth occurring more frequently in patients receiving exogenous progesterone (random-effects modelling, RR 1.76, 95% CI 1.29 to 2.40, p<0.001, number needed to treat 11).^16^ An updated and extended literature search and meta-analysis by Casarramona *et al*, in which four additional studies were included compared with the previous review in 2017, found comparable results to the Green review (single cycle; live birth rate RR 2.47, 95% CI 1.37 to 4.44; three randomised controlled trials (RCTs), 678 participants; cumulative live birth rate for up to six cycles: RR 1.49, 95% CI 1.17 to 1.90; five RCTs, 1027 participants).^17^ For both reviews, the level of evidence had been graded low to moderate. The studies in the meta-analysis are often single-centre based, fail to obtain individual power, were mostly not (double-) blinded, included only a single treatment cycle and/or evaluated various types of luteal support. Due to the overall moderate study quality and small to moderate size of the individual studies, the certainty of the evidence should be considered with caution and broad implementation of progesterone luteal support in MOH-IUI treatment cannot be justified with the current research data. The substandard evidence quality warrants a large, well-designed, well-powered trial to provide the evidence that is needed to confirm or dismiss the effect of progesterone LPS after MOH-IUI. For this purpose, the LUMO (LUteal phase support in Mild Ovarian hyperstimulation (MOH) for intra-unterine insemination (IUI)) study was designed, funded and is currently ongoing.

The primary aim of the LUMO study is to determine whether the addition of exogenous progesterone in the luteal phase of MOH-IUI treatment will lead to increased live birth rates and will provide the basis for application of this strategy in daily practice. The hypothesis is that the chance of pregnancy leading to live birth within a 6-month study period will increase from 30% to 39% after MOH-IUI treatment with LPS. In addition, the study seeks to evaluate the total budget impact of the addition of LPS in MOH-IUI treatment in terms of reduction in total budget spent on (in)fertility care through a cost-effectiveness analysis.

## Methods and analysis

### Design and setting

The LUMO study is a multicentre, double-blind, randomised-controlled trial with cost-effectiveness analysis. It is coordinated by the UMC Utrecht, Netherlands, and will be performed within the Dutch Consortium for Healthcare Evaluation and Research in Obstetrics and Gynecology. There are two treatment arms (A LPS; B placebo, non-crossover). All initiated MOH-IUI cycles within 6 months after randomisation are included (study period). Follow-up period ends 12 months after the end of the study period (18 months after randomisation). The primary outcome is cumulative pregnancy, achieved within 6 months after randomisation, leading to live birth rate. The aim is to include 1008 patients (504 patients in each group).

At present, there are 33 sites (fertility clinics, academic and non-academic hospitals) participating in the LUMO study. All participating sites and their corresponding local principal investigator are mentioned in the ‘Acknowledgements’ section.

### Eligibility criteria

Eligibility criteria are in line with the indication for MOH-IUI treatment and in accordance with current (Dutch) NVOG (Nederlandse Vereniging voor Obstetrie en Gynaecologie (Dutch Sciety for Obestrics and Gynaecology)guidelines.^18^ In the Netherlands, in couples with unexplained subfertility, the prognosis for spontaneous pregnancy in the year following the subfertility workup is calculated using the validated Hunault prognostic model.^19^ This model uses the predictive factors female age, subfertility duration, type of subfertility (primary vs secondary), sperm motility and referral status. When the likelihood of spontaneous pregnancy is <30% (or ≥30% after an expectant management period of at least six additional months), MOH-IUI is suggested as the primary treatment. To participate in the study, a participant must meet all of the following criteria: (1) diagnosis of unexplained subfertility; (2) Hunault <30% (or ≥30%, after an expectant management period of at least six additional months); (3) female age 18–43 years; (4) female body mass index (BMI) <45 kg/m^2^; (5) primary or secondary subfertility, for at least a period of 1 year (or, in case of secondary infertility with previous successful MOH-IUI treatment, an expectant management of at least 6 months); (6) regular menstrual cycle; (7) total motile sperm count >10 million (prewash/unprocessed) and (8) first MOH-IUI cycle (with gonadotropins), with the intent to receive this treatment for at least 6 months. Exclusion criteria are (1) uncorrected uterine factors, such as endometrial polyps or submucosal fibroids; (2) insufficient knowledge or understanding of the Dutch or English language and not willing or able to receive study information via a certified translator; (3) not able or willing to provide (written) informed consent and (4) contraindications for vaginal progesterone, particularly females with allergy to peanuts or soya.

### Study procedures

#### Recruitment and randomisation

Potential participants can be informed about the existence of this trial by their treating doctor if they meet eligibility criteria. For additional information, patients will be referred to the websites of UMC Utrecht, Freya (patient federation) and Zorgevaluatie Nederland. More extensive information will be included in the patient information form (PIF) that patients will receive as they expressed their potential interest in participating. After receiving the PIF, the research nurse or researcher of the participating research site will contact potential participants to check for any remaining questions and ask if they indeed want to participate. After obtaining written informed consent (signed by both the female patient and her partner), randomisation will be performed by the pharmacy of the UMC Utrecht using computer-generated randomisation at a ratio of 1:1 into two treatment groups. The researchers and participants will not be informed about the randomisation outcome until the trial is completed, and the database is locked.

#### Study medication

The study medication (Utrogestan) 300 mg or placebo 300 mg, vaginal capsules (soft), are provided by Besins Healthcare. The capsules are packed in white high-density polyethylene bottles of 15 capsules, with a white polypropylene child-resistant screw cap. The capsules are oblong yellowish, soft gelatin, approximately 2.5 cm × 0.8 cm, containing a whitish oily suspension. The excipient is soyabean lecithin (3 mg per capsule) and sunflower oil (refined). The capsule shell excipients are gelatin, glycerol, titanium dioxide and water. The manufacture and control of the placebo are essentially the same as for the active, but without progesterone drug substance and with appropriately compensating quantities of some excipients.

Utrogestan is a commonly administered medicine in fertility treatment worldwide and is registered in the European Union (EU) for use in assisted reproductive techniques (ART) cycles (Marketing Authorisation number 60954, 1 June 2021). The overall toxicological and safety profile of the progesterone products is well established. Potential side effects (vaginal discharge, mild stomachache, headache or fatigue) are well known, and the use of micronised progesterone is proven to be safe during (early) pregnancy for both mother and child.

#### Accountability

The pharmacy of the UMC Utrecht will keep drug accountability according to local standard operating procedures and national regulation drug accountability. Compliance to therapy is measured via online diaries sent to participants. The pharmacy of the UMC Utrecht will distribute the study medication to the participants’ home address. Upon approval by Besins Healthcare, undistributed study medication will be destructed at the UMC Utrecht. Unused medication (delivered to participants) can be handed in at any local pharmacy, where the medication will be destructed. A summary of the product characteristics (SmPC) of Utrogestan 300 mg is provided as online supplemental file 1.

#### Concomitant therapy

Concomitant medications are allowed as far as they are safe for usage in a subsequent pregnancy. Progesterone may affect the working mechanism of other medicines, and other medicines may affect the metabolism of progesterone. Therefore, the prescribing physician will ensure that the possibilities of drug interaction will be inventoried and appropriate measures will be taken if co-medications as mentioned in the SmPC are used.

#### Study timeline

MOH-IUI treatment is conducted according to local treatment protocols. Women assigned to the intervention group will start LPS, applying a daily dosage of 2dd 300 mg Utrogestan in vaginal capsules on the second day after IUI (IUI+2 days). Women assigned to the control group will daily start medication of 2dd 300 mg vaginal capsules with placebo, also on the second day after the IUI. Treatment is continued until the onset of menstruation, a negative pregnancy test, miscarriage or until 7 weeks of gestation. Figure 1 presents an overview of the procedures that participants will undergo during standard MOH-IUI treatment and additional actions required for the LUMO study.

**Figure 1 F1:**
[figure not shown]
Overview of the main procedures that participants will undergo during standard MOH-IUI treatment and additional actions required for the LUMO trial. BMI, body mass index; FSH, follicle-stimulating hormone; HCG, human chorionic gonadotropin; IUI, intrauterine insemination; LH, luteinising hormone; MOH, mild ovarian hyperstimulation; VCM, total motile sperm count.

The study period is 6 months. Study medication is used after all MOH-IUI treatment cycles within this period. The follow-up period includes the subsequent 12 months after the end of the study period. During the study period and follow-up period, participants do not need to visit the hospital more frequently. There are no additional examinations or blood tests in addition to standard care. No invasive procedures need to be performed. Study participation ends 18 months after randomisation.

A total of three questionnaires will be sent during the study period. At randomisation, questionnaire 1 (Q1) will be sent that contains questions regarding quality of life (FertiQoL). 6 months after randomisation, questionnaire 2 (Q2) will be sent. This questionnaire contains questions regarding quality of life (FertiQoL), compliance to therapy and side effects. Questionnaire 3 (Q3) will be sent 18 months after randomisation. In the case of an ongoing pregnancy within the study period, questionnaire Q3A is sent that contains questions about the pregnancy (complications), delivery and perinatal outcomes. Questionnaire Q3B is sent in case a couple did not achieve an ongoing pregnancy during the study period. This questionnaire contains questions regarding information on the use of additional ART. After every MOH-IUI cycle during the study period, the online medication diary keeps track of compliance to therapy and side effects.

#### Withdrawal

Participants can leave the study at any time for any reason if they wish to do so, without any consequences. The investigator can decide to withdraw a participant from the study for urgent medical reasons. In the case of withdrawal of consent, outcomes will be imputed using all information obtained before withdrawal of consent.

#### Unblinding

In case of a medical emergency requiring unblinding, the pharmacy of the UMC Utrecht will provide a 24/7 backup service. The decision to unblind is at the discretion of the local investigator. If applicable, unblinding information will be accessible to people who need to be involved in the safety reporting to the European Medicines Agency, Data Safety Monitoring Boards (DSMB) or people performing ongoing safety evaluations during the clinical trial.

### Outcomes

The primary outcome is cumulative pregnancy achieved within 6 months after randomisation, leading to live birth rate. Secondary outcomes include (1) progression to in vitro fertilisation (IVF); (2) multiple pregnancy rate; (3) time to pregnancy leading to live birth; (4) pregnancy complications (ie, hypertensive pregnancy disorders, blood loss during early pregnancy, preterm delivery); (5) perinatal outcomes (ie, stillbirth, birth weight, gestational age at delivery, congenital anomalies); (6) delivery outcomes (ie, type of delivery: spontaneous/induced, vaginal/caesarean, blood loss >1 L during delivery, manual removal of placenta); (7) side effects (incidence of common side effects: headache, vaginal discharge/itching, stomach ache, fatigue, nausea and uncommon/other side effects); (8) compliance to therapy; (9) quality of life; (10) number of adverse events (AEs) and serious adverse events (SAEs); and (11) cost-effectivity.

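### The side-effect outcome mixes capsule effects with symptoms of early pregnancy, so its relative risk can exceed 1 without any capsule effect, mainly for nausea and in the first-cycle analysis.

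*Protocol article*

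**What the plan says.** Outcomes lists as the seventh secondary outcome "side effects (incidence of common side effects: headache, vaginal discharge/itching, stomach ache, fatigue, nausea and uncommon/other side effects", with no split by pregnancy status. Data collection and data analysis expresses primary and secondary outcomes as relative risks with 95% CIs, per patient and per (first) cycle, and names no exposure-time denominator.

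Capsules start "in vaginal capsules on the second day after the IUI procedure" (Abstract). On stopping, Study timeline says: "Treatment is continued until the onset of menstruation, a negative pregnancy test, miscarriage or until 7 weeks of gestation". The Abstract dates the test: "a negative pregnancy test (IUI+14 days), a miscarriage or until 7 weeks of gestation in case of a viable pregnancy". The same rule applies in both arms.

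Side effects are collected twice. On the month-6 questionnaire (Q2), Study timeline says: "This questionnaire contains questions regarding quality of life (FertiQoL), compliance to therapy and side effects". On the diary it says: "After every MOH-IUI cycle during the study period, the online medication diary keeps track of compliance to therapy and side effects". The strengths and limitations box says that "participants will receive an online medication diary at the start of every cycle".

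Study medication gives the product's known effects: "Potential side effects (vaginal discharge, mild stomachache, headache or fatigue) are well known". Nausea is not among them, yet Outcomes counts it as a common side effect.

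**The concern.** Nausea, fatigue, stomach ache and headache also occur in early pregnancy. The trial expects 30% of the placebo arm and 39% of the progesterone arm to conceive a pregnancy leading to live birth within six months (Introduction, Sample size). An undivided count of these symptoms therefore carries part of the efficacy effect into the tolerability result. The month-6 questionnaire has the same feature, because by then the arms are expected to differ in how many women are or have been pregnant.

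At stake is how the result is read. The Discussion rests a possible recommendation after every MOH-IUI cycle partly on a favourable safety profile. An excess of nausea that comes from extra pregnancies could be reported as a drug effect.

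**Working it through.** The article states no symptom rate and no expected side-effect relative risk, so there is no figure of its own to reproduce. The check asks what relative risk the stated analysis would show if the capsules caused no symptoms.

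**Inputs from the article.** Six-month rates are 30% and 39%. They are pregnancies leading to live birth, used here as the conception rates. Capsules run from IUI+2 to IUI+14 without conception and to 7 weeks of gestation with it. The planned size is 504 per arm.

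**Assumptions.** IUI falls at gestational week 2+0. There are K = 4, 5 or 6 cycles with constant per-cycle conception p. The chance of reporting a symptom is s in a non-conception cycle and t in the conception cycle, the same in both arms.

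**Step 1: exposure.** IUI+2 to IUI+14 is 13 days. IUI+2 to IUI+35 is 34 days, 2.6 times as long. But conception ends further cycles. With P the six-month rate, p = 1 - (1 - P)^(1/K), mean cycles are P/p, and mean treated days are 13 x (mean cycles - P) + 34 x P.

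- K = 4, placebo: 13 x (3.517 - 0.30) + 34 x 0.30 = 52.0
- K = 4, progesterone: 13 x (3.355 - 0.39) + 34 x 0.39 = 51.8
- K = 5: 62.9 vs 62.1
- K = 6: 73.9 vs 72.3

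Suppose risk follows exposure time only, with s = 0.10 and t = 1 - 0.90^(34/13) = 0.24. The relative risk is then 0.98-1.00 per patient and 1.03-1.04 in the first cycle.

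**Step 2: added pregnancy symptoms.** The first-cycle rate is s + p(t - s). The per-patient rate is 1 minus the sum over k = 1..K of (1 - p)^(k-1) p (1 - s)^(k-1) (1 - t), minus (1 - p)^K (1 - s)^K.

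Example with K = 5, s = 0.02, t = 0.60, where p = 1 - 0.70^(1/5) = 0.0689 and 1 - 0.61^(1/5) = 0.0941:

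- First cycle: 0.02 + 0.0689 x 0.58 = 0.060 and 0.02 + 0.0941 x 0.58 = 0.075. The relative risk is 1.25 (1.245 before rounding).
- Per patient: 0.252 and 0.298. The relative risk is 1.18 (1.185 before rounding).

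A simpler woman-level mixture gives nearly the same. With 60% of pregnant and 10% of other women reporting, 0.39 x 0.6 + 0.61 x 0.1 = 0.295 against 0.30 x 0.6 + 0.70 x 0.1 = 0.250, a relative risk of 1.18 (95% CI at 504 per arm 0.96-1.45). Its 10% over six months is about 2% per cycle over five cycles.

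**Step 3: range** (t = 0.50-0.80, K = 4-6).

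| s per non-conception cycle | First-cycle RR | Per-patient RR |
|---|---|---|
| 1% | 1.27-1.32 | 1.21-1.26 |
| 2% | 1.21-1.28 | 1.15-1.22 |
| 5% | 1.13-1.20 | 1.07-1.15 |
| 10% | 1.07-1.14 | 1.02-1.09 |
| 20% | 1.03-1.07 | 0.99-1.03 |
| 30% | 1.01-1.05 | 0.98-1.01 |

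The relative bias is larger in the first cycle. The absolute excess is larger per patient: for s of 1-10% it is 0.9-2.4 points in the first cycle and 1.1-6.9 points per patient.

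**Step 4: precision.** At 504 per arm and these expected rates, every first-cycle 95% CI includes 1. The per-patient CI excludes 1 only for s of 1-2% with t of 70-80%. The most extreme case (K = 4, s = 1%, t = 80%) gives 1.26 (1.04-1.52).

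**The case against.** A reader might infer that the arm with more pregnancies is bound to show more side effects. The documents do not support that. Women who do not conceive go on to further treated cycles and diaries, so treated days nearly balance, and for symptoms reported in 20-30% of cycles the per-patient relative risk is near 1 or slightly below. The 2.6-fold exposure compares single cycles and does not carry over to the six-month comparison. The bias also needs a real difference in pregnancies.

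A reader might also infer that the two diary statements contradict each other. They need not: one says when the diary is received, the other when it tracks use and symptoms. What remains is an ambiguity about whether symptoms are dated, or recorded only once the woman may know her result. The diary itself is not shown.

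Two further objections have force. The blinded comparison under identical stopping rules is a valid total effect of assignment; only reading it as capsule tolerability goes wrong, and the article does not say it will be so read. And tables by cycle or pregnancy status are often left to an analysis plan, which is not shown here. But the article does fix the outcome wording and the plain relative risk, and no later table can recover symptom timing that was not collected.

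**Conclusion.** The point holds in limited form. As defined and analysed, the outcome cannot separate capsule effects from symptoms of early pregnancy. With the hypothesised 30% vs 39% and no capsule effect, the spurious relative risk is about 1.07-1.32 in the first cycle and 1.02-1.26 per patient when symptoms are reported in 1-10% of non-conception and 50-80% of conception cycles. It matters most for symptoms uncommon outside pregnancy, nausea above all. For symptoms common in every cycle the per-patient bias is negligible or slightly reversed, and longer exposure alone gives no per-patient excess. In most scenarios the confidence interval would include 1.

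All symptom rates, the number of cycles and the constant conception rate are assumptions. So is equating conception with pregnancy leading to live birth; conceptions that end in miscarriage are left out. This is a cheap improvement to interpretation and leaves the primary outcome untouched.

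**What to change.** 1. Keep the planned per-patient relative risk and label it the total effect of assignment.
2. Prespecify, as the capsule-tolerability comparison, diary symptoms from IUI+2 to IUI+14 in the first treated cycle, before the pregnancy result is known, with all cycles as support. Randomisation protects the first treated cycle.
3. Report symptoms from IUI+15 to 7 weeks separately and only descriptively, because pregnancy is a post-randomisation event that treatment is expected to change.
4. Treat the month-6 side-effect answers as supportive.
5. State, in the strengths and limitations box and in Study timeline alike, that the diary opens at cycle start and records dated symptoms.

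The cost is outcome wording and a date cut in an existing diary, with no new procedure; recruitment is still under way (Study status). The downside is real. The 13-day window is about 18-25% of mean treated days (13/73.9 to 13/51.8), so the comparison is less precise and does not describe tolerability in gestational weeks 4 to 7. It also depends on diary entries that can be dated.
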